## Abstract

**Background:**

We aim to obtain clinical trial data regarding the safety, efficacy, and usefulness of invasive laser acupuncture (ILA) for non-specific chronic low back pain (NSCLBP) through a randomized placebo-controlled trial.

**Methods:**

Our clinical trial will be an assessor- and patient-blinded, prospective, parallel-arm, multi-center, randomized placebo-controlled clinical trial. One hundred and six participants with NSCLBP will be allocated evenly to the 650 ILA or control group. All participants will receive education on exercise and self-management. The 650 ILA group will undergo 650 nm ILA for 10 min, and the control group will undergo sham ILA for 10 min per visit, twice a week for 4 weeks, at bilateral GB30, BL23, BL24, and BL25. The primary outcome will be the proportion of responders (≥30% reduction in pain visual analogue scale [VAS] without increased use of painkillers) at 3 days after the intervention ends. The secondary outcomes will include changes in the scores of the VAS, European Quality of Life Five Dimension Five Level scale, and Korean version of the Oswestry Disability Index at 3 days after the intervention ends and 8 weeks after the intervention ends.

**Discussions:**

The results of our study will provide clinical evidence concerning the safety and efficacy of 650 nm ILA for the management of NSCLBP.

**Clinical trial registration:**

https://cris.nih.go.kr/cris/search/detailSearch.do?search_lang=E&focus=reset_12&search_page=M&pageSize=10&page=undefined&seq=21591&status=5&seq_group=21591, identifier KCT0007167.

## Introduction

Low back pain (LBP), defined as discomfort and pain, localized below the costal margin and above the inferior gluteal folds with or without referred lower extremity pain, is a symptom rather than a specific disease (1, 2). It is a major cause of disability in daily living. Functional restrictions and consequent disabilities pose a huge economic burden for individuals and the society (3). Most LBPs are non-specific (commonly cited as 90–95%) (4), and non-specific chronic LBP (NSCLBP) is defined as that which cannot be attributed to a known specific pathology (e.g., structural deformity, tumor, osteoporosis, infection, radicular syndrome, fracture, cauda equina syndrome, or ankylosing spondylitis) and persists for >3 months (1, 2, 5–7).

Treatment guidelines for patients with NSCLBP recommend the use of exercise therapy, antidepressants, psychosocial interventions, and non-steroidal anti-inflammatory drugs (2, 5, 6). Non-pharmacological treatments, such as exercise and self-management, are preferred to pharmacological interventions in the management of NSCLBP (2, 7–9). Physical modalities such as transcutaneous electrical nerve stimulation and low level laser therapy (LLLT) have a low quality evidence (6, 8) and acupuncture has mixed support and received conflicting recommendations (2, 5, 8).

Low level laser therapy is a light source intervention that creates no vibration, heat, or sound and stimulates photochemical or non-thermal cellular processes (10). LLLT is currently used to treat musculoskeletal disorders, such as back pain (11). The possible underlying mechanisms for the pain reduction effects of LLLT include its inhibition of neural function, anti-inflammatory effect, and connective tissue repair ability which have been demonstrated by a number of experiments (12–14). Laser acupuncture (LA) is the irradiation of a low-intensity laser at the acupoints using laser pointer devices (15). Whether LLLT, including LA, is effective for LBP when compared with sham laser remains controversial. A Cochrane systematic review of LLLT on non-specific LBP in 2008 decried the lack of sufficient data to either refute or support the efficacy of LLLT for the management of LBP (16). In contrast, a meta-analysis suggested that LLLT was an effective treatment for reducing pain in patients with NSCLBP (17, 18). Glazov et al. reported that LLLT alone or in combination with other therapies might effectively reduce pain for up to 3 months in NSCLBP without adverse effects (19).

While LA is a non-invasive therapy that uses laser-emitting devices, invasive LA (ILA) is conducted concurrently with invasive acupuncture and focused laser irradiation utilizing an acupuncture needle attached to a laser instrument (20). Our previous pilot randomized controlled trial (RCT) revealed that 650 nm ILA with the same ILA parameters (650 nm wavelength, 20 mW power, and 50 Hz frequency), treatment acupoint, and treatment schedule as in this study significantly improved pain and pain-related functional limitations in patients with NSCLBP at the end of the intervention (21). These potential effects of 650 nm ILA on NSCLBP requires validation using a rigorous RCT with a large sample size. Therefore, we aim to obtain clinical evidence on the safety and efficacy of 650 nm ILA for the management of NSCLBP. In a situation where is no high-quality evidence supporting the efficacy of LLLT and acupuncture, the results of this study will provide clinical evidence of the use of ILA for NSCLBP and thus promote the use of ILA in the treatment of NSCLBP.

## Materials and analysis

### Aims

1)We will investigate the clinically persistent pain-reduction effect of 650 nm ILA for NSCLBP at 3 days after the end of intervention.2)We will investigate the pain reduction, functional limitation improvement, and quality of life improvement effects of 650 nm ILA for NSCLBP.3)We will investigate the safety of 650 nm ILA in patients with NSCLBP.

### Hypothesis

1)The 650 ILA group will have a significantly higher proportion of responders than the control group at 3 days after the end of intervention.2)The 650 nm ILA will show improvements in pain intensity, quality of life, and functional limitation in patients with NSCLBP.3)The 650 nm ILA would be a safe treatment for patients with NSCLBP.

### Study design and setting

Our study was approved by the Ministry of Food and Drug Safety (Medical Device Approval No. 1322) and was registered with the Clinical Research Information Service (registration No. KCT0007167). Our study complies with the Korean Good Clinical Practice guidelines and the principles of the Declaration of Helsinki. We have written the manuscript in accordance with the Standard Protocol Items: Recommendations for Interventional Trials (SPIRIT) reporting checklist (22).

This clinical trial will be an assessor and patient–blinded, prospective, parallel-arm, multi-center, randomized placebo-controlled clinical trial. In total, 106 eligible participants will be randomized evenly into the 650 ILA or control group (*n* = 53 in each group). All participants will receive education on exercise and self-management. Participants in the 650 ILA group will undergo real 650 nm ILA for 10 min, while those in the control group will undergo sham ILA for 10 min. The treatment will be administered once per visit, twice a week for 4 weeks, at bilateral Gallbladder 30 (GB30; Huantiao), Bladder 23 (BL23; Shenshu), Bladder 24 (BL24; Qihaishu), and Bladder 25 (BL25; Dachangshu).

The primary outcome will be the proportion of responders (≥30% reduction in pain visual analogue scale [VAS] without increased use of painkillers) at 3 days after the intervention ends. The secondary outcome will be changes in the scores of the VAS, European Quality of Life Five Dimension Five Level scale (EQ-5D-5L), and Korean version of the Oswestry Disability Index (ODI) at 3 days after the intervention ends and 8 weeks after the intervention ends.

The clinical trial design is shown in Table 1.

**TABLE 1 T1:** SPIRIT statement showing the enrollment, interventions, and data collection.

	Study period							
	Enrollment	Allocation	Post-allocation					Close-out
Timepoint	Screening		Visit 1–2	Visit 3–4	Visit 5–6	Visit 7–8	Visit 9	Visit 10
	Week		1	2	3	4	4 + 3 days	12
**Enrollment**								
Informed consent	X							
Sociodemographic profile	X							
Medical history	X							
Vital signs	X	X	X	X	X	X	X	X
Inclusion/Exclusion criteria	X							
Allocation		X						
Visual analogue scale	X							
**Interventions**								
Invasive laser acupuncture (sham or 650 nm)			X	X	X	X		
Education on self management and exercise			X	X	X	X		
**Assessments**								
Change of medical history			X	X	X	X	X	X
Safety assessment (Incidence of AEs)			X	X	X	X	X	X
Clinical laboratory test	X						X	
Visual analogue scale			X				X	X
European quality of life five dimension five level scale			X				X	X
Scores for the Korean version of the Oswestry disability index level scale			X				X	X

### Recruitment

We will recruit participants at the Kyung Hee University Korean Medicine Hospital and Dongshin University Gwangju Korean Medicine Hospital in the Republic of Korea *via* the use of posters, local newspapers, and the internet in hospitals and communities. Interested people will receive an explanation of this study from the clinical research coordinator (CRC) upon visiting the hospital and will provide written informed consent prior to participation.

At each visit, the CRC will explain the following visit schedule and will adjust the visit schedules for each participant to facilitate participation.

### Inclusion criteria

(1) Adults aged between 19 and 70 years; (2) has NSCLBP lasting for at least the preceding 3 months, and LBP that occurred more than 14 days a month; (3) has no change in history of medications for 4 weeks before screening. For participants with medications prescribed and used for NSCLBP, usage shall be at a stable dose in the 4 weeks prior to the baseline visit; (4) moderate pain (100 mm VAS scores for pain had a range of 35–74) (23) at screening; and (5) has sufficient fluency in Korean to perform valid assessments.

### Exclusion criteria

(1) Participants has progressive neurological deficits or radicular pain; (2) has a serious disease (diabetic neuropathy or cancer, severe kidney, liver, cerebrovascular, or cardiovascular disease); (3) has a serious spinal pathology (cauda equina syndrome, cancer, inflammatory spondylitis, recent vertebral fracture, or spinal infection); (4) has a LBP caused by rheumatoid arthritis, ankylosing spondylitis, gout, trauma, or fibromyalgia; (5) has a history of treatment for mental illness (depression, dementia, schizophrenia, or epilepsy) or drug/alcohol dependency in the 6 months preceding screening; (6) has moderate or severe depression (scored ≥ 23 points on a Korean version of Beck depression inventory-II) (24) at screening; (7) has contraindications for ILA, such as presence of electronic medical devices, severe skin disease in the lumbar region, blood clotting abnormalities, or presence of metallic devices in the lumbar vertebrae; (8) has a history of lumbar spinal surgery within 1 year or scheduled procedures during the trial; (9) participation for the purpose of social insurance or compensation; (10) concurrent participation in another trial; (11) Pregnant or having a plan for pregnancy; and (12) not suitable for ILA and our rescue regimen.

### Dropout and violation criteria

The dropout criteria are as follows: (1) incomplete data that can affect the results of the trial; (2) decision to discontinue participation in this trial by the institutional review board (IRB) or principal investigator (PI) owing to the inability of the participant to participate in this study or the occurrence of a side effects requiring long-term treatment; (3) withdrawal of consent; or (4) occurrence of a serious adverse event (SAE) causing requirement of hospitalization or surgery, serious disability, or death. Participants who meet the dropout criteria will be discontinued from participating in our clinical trial.

The violation criteria are as follows: (1) participating in less than six of the eight treatment sessions (<75% compliance with the intervention protocol); and (2) serious deviation in implementation or critical errors in the protocol.

The participants who meet the violation and dropout criteria will be excluded from the per protocol set (PPS) analysis.

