### Sample size estimation

In our previous pilot study (21), the difference in proportion of responders between 650 ILA (93% [14/15]) and control groups (40% [6/15]) was 53%. To obtain sufficient clinical data, we determined the sample size assuming an expected responder proportion of 30% in the control group and 60% in the 650 ILA group, a two-sided alpha level of 0.05, and a statistical power of 0.8. Under these assumptions, a total of 84 (42 per group) participants will be required. Estimating a maximum dropout rate of 20%, 106 participants (53 in each group) will be required in our trial.

$$\frac{n={\left(z_{\alpha /2}\,\sqrt{2\,\bar{p}\,\bar{q}}+z_{\beta }\,\sqrt{p_{1}\,q_{1}+p_{2}\,q_{2}}\right)}^{2}}{{\left(p_{t}-p_{c}\right)}^{2}}=\frac{{\left(1.96\,\sqrt{2\times 0.45\times 0.55}+0.842\,\sqrt{0.30\times 0.70+0.60\times 0.40}\right)}^{2}}{{\left(0.60-0.30\right)}^{2}}\approx 42$$

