### Statistical analysis

The final data will be analyzed by a biostatistician not involved in the execution of our trial. The primary analysis population for assessing the efficacy of the intervention will be a full analysis set (FAS), while the supplementary analysis population will be a PPS. The results of the FAS and PPS analyses will be compared and reflected in the efficacy evaluation. “Multiple Imputation” method will be used to obtain the missing value. All analyses will be performed at the 5% (two-sided) significance level using SAS^®^ version 9.4 (SAS institute. Inc., Cary, NC, USA) software. We will not perform interim analyses.

Baseline characteristics and variables will be compared between the two groups. Categorical data will be compared using the Fisher’s exact test or chi-square test, while continuous data will be compared using the Wilcoxon’s rank sum test or independent *t*-test.

The difference in responder proportions will be tested using the chi-square test or Fisher’s exact test. The degrees of changes in the VAS, EQ-5D-5L, and ODI scores at 3 days after the treatment ends and 8 weeks after the intervention ends, relative to the baseline score, between the groups will be evaluated using analysis of covariance with baseline scores as covariates. Within each group, changes in VAS, EQ-5D-5L, and ODI scores at each time will be analyzed using one-way analysis of variance and a paired *t*-test or Wilcoxon signed rank test. Sub-analyses will be performed according to each institution.

A safety assessment will be conducted for all SAEs and AEs that will occur during the trial period. The incidences of SAEs and AEs will be compared between the two groups using chi-square test or Fisher’s exact test. A comparative analysis will be carried out between the groups for participants who will be out of normal range for a clinical laboratory test.

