Considering the results of this study, 650 nm ILA is expected to show safety, clinically significant improvement, pain reduction, and improvement of functional limitation and quality of life in patients with NSCLBP. This is important for the clinical use of 650 nm ILA and development of optimal laser parameters for the treatment of NSCLBP.

This protocol has certain limitations. First, we will not use different treatment methods of LA for NSCLBP treatment. The factors that influence the efficacy of LA are selected acupoints, wavelength, and energy dose. Various treatment methods of LA differ according to wavelength, energy dose, and acupoints for treating NSCLBP (16–19, 38). Since 650 nm ILA parameters, including the wavelength, power, energy dose, and acupoints, used in our pilot study show significant pain reduction at the intervention endpoint, we adopted only the 650 nm ILA parameters used in our pilot study in this study. Thus, further studies should be conducted to investigate the optimal parameters. Second, since most participants in our pilot study had moderate pain at the baseline and the high dropout rate owing to pain increase during the study period in the case of patients with severe pain was concerning, our study will include only patients with moderate NSCLBP, not those with severe NSCLBP. Third, since the practitioner will operate the laser emitting device according to the treatment method of each group (650 ILA group, 20 mW power for 10 min; control group, 0 mW power for 10 min), we cannot adopt practitioner blinding. Therefore, we will adopt an assessor- and patient-blinded study design.

Nevertheless, the findings of this study would suggest clinical evidence concerning the safety and efficacy of 650 nm ILA for the management of NSCLBP, thereby establishing the basis for further investigation. It would contribute to increasing the availability of laser and promoting the development of optimal laser treatment method in the management of LBP.

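### The dropout rule ends trial participation as well as treatment, so participants removed before Visit 9 lose a primary outcome that multiple imputation has little data to replace

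*Protocol article*

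**What the plan says.** The section on dropout and violation criteria lists four grounds for dropout. One is "incomplete data that can affect the results of the trial". Another is a decision by the ethics board or principal investigator, for reasons that include "the occurrence of a side effects requiring long-term treatment". The others are withdrawal of consent and "occurrence of a serious adverse event (SAE) causing requirement of hospitalization or surgery, serious disability, or death". The consequence is the same for all four: "Participants who meet the dropout criteria will be discontinued from participating in our clinical trial". On analysis, the section adds: "The participants who meet the violation and dropout criteria will be excluded from the per protocol set (PPS) analysis".

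The statistical analysis section makes the full analysis set primary. On missing data it says only that a multiple imputation "method will be used to obtain the missing value", with no exception by reason.

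The outcome section defines a responder by a 30% fall in VAS without more painkiller use, assessed 3 days after treatment ends (Visit 9). Discontinuation plays no part in that definition. Table 1 shows the VAS at screening, in the Visit 1–2 column, at Visit 9 and at Visit 10, and nowhere between.

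**The concern.** The rule itself creates missing primary outcomes. Someone who stops treatment because of harm could still be asked for a VAS score and painkiller use at Visit 9, but as written that person has left the trial. If those who leave tend to be people who would not have responded, imputing them from completers of the same arm overstates response. If the arms lose different numbers, the comparison is distorted too.

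Three features make this harder to repair later:

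- With no VAS at Visits 3 to 8, an imputation model for someone removed during treatment has essentially baseline data and arm to work with. An analysis plan cannot recover data that were never collected.
- The sections do not fit together. Taking more painkillers counts as failure, while leaving because of harm has no stated status and could be imputed as success.
- The incomplete-data criterion is circular. It answers missing data by removing the participant, which makes more data missing.

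**Working it through.** **Plan's own figure.** Inputs from the sample size section: 30% versus 60% response, two-sided 5%, power 80%, up to 20% dropout.

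n = (1.96·√(2×0.45×0.55) + 0.842·√(0.30×0.70 + 0.60×0.40))² / 0.30² = 41.98, so 42 per arm. 42/0.80 = 52.5, so 53 per arm and 106 in total. The stated size reproduces.

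**Effect on the estimate.** Assumptions (not in the article): imputation is missing-at-random within arm, so its expected result is the completer rate; completers respond at 60% and 30%; every dropout is a non-responder. Then true rate = completer rate × (1 − dropout).

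| Dropout ILA / sham | True rates | True difference | Imputed difference |
|---|---|---|---|
| 10% / 10% | 54% v 27% | 27 points | 30 points |
| 20% / 20% | 48% v 24% | 24 points | 30 points |
| 20% / 5% | 48% v 28.5% | 19.5 points | 30 points |
| 5% / 20% | 57% v 24% | 33 points | 30 points |

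The last row runs against the laser arm. If dropouts are counted as non-responders at 48% v 24% with 53 per arm, exact chi-square power is 75.0% (73.7% by the normal approximation), below the planned 80%.

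**Effect on type I error.** Assume a true response of 40% in both arms, all dropouts failures, 53 per arm. Completer rate = 0.40/(1 − dropout). At 25% / 10% this gives 0.40/0.75 = 53.3% and 0.40/0.90 = 44.4%, a false difference of 8.9 points. Simulated rejection rates:

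| Dropout ILA / sham | Completer rates | Completer-based test | Imputation by arm, Rubin's rules |
|---|---|---|---|
| 20% / 20% | 50.0% v 50.0% | about 5% | 6.0% |
| 25% / 15% | 53.3% v 47.1% | 8.9% | 10.7% |
| 25% / 10% | 53.3% v 44.4% | 13.1% | 14.7% |
| 30% / 10% | 57.1% v 44.4% | 21.5% | 22.6% |

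The unequal splits average 20%, 17.5% and 20% over the two arms, within the plan's 20% maximum. Swapping the arms gives the same error rates with the false difference favouring sham. Counting dropouts as non-responders holds 5.0–5.3% here, but only because the scenario makes all of them non-responders.

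**A milder scenario.** If half the dropouts fail and the rest respond like completers, imputation rejects 7.0% at 25% / 10% and 7.4% at 30% / 10%. Coding all of them as non-responders gives 6.8% and 8.4%. Neither method is then neutral.

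**The case against.** A reader might infer that the plan credits treatment failures with the completers' response rate. The article does not say so. It names multiple imputation without a model, a missingness assumption or sensitivity analyses, all of which may sit in an analysis plan that is not shown. Nor does it call these participants failures: withdrawal of consent, a missing form or an unrelated hospital admission says little about back pain. This objection stands, so the bias is conditional.

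A reader might also take the remark in the Discussion that "the high dropout rate owing to pain increase during the study period in the case of patients with severe pain was concerning" as evidence of outcome-related dropout in this trial. It explains why people with severe pain are not enrolled. It shows that the authors link pain to dropout, not that such loss is expected among the moderate-pain participants.

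The unequal dropout splits have no support in the documents, and the pilot reported no adverse events associated with laser irradiation. Loss through harm may be rare, and with balanced dropout the type I error is close to nominal.

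Two further strong readings fail. One is that safety data are lost for those harmed. The adverse events and statistical sections record and assess all events during the trial, so only follow-up after removal could be affected. The other is that the incomplete-data criterion lets someone select participants by their results. Only the practitioners and those managing the codes are unblinded, the stated exclusion concerns the supplementary per-protocol set, and nothing removes anyone from the full analysis set.

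None of this answers the central point: the article states that participation ends, and no analysis plan can restore a Visit 9 measurement that was not taken.

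**Conclusion.** The point holds as a defect in how follow-up and the primary endpoint are fixed. The protocol ends participation where ending treatment would suffice, and so creates avoidable, possibly informative gaps in the primary outcome. It then names a remedy that has no VAS from Visits 3 to 8 to draw on. Participants removed after Visit 9 are unaffected for the primary endpoint.

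The size cannot be fixed from the documents. It depends on a default missing-at-random imputation, on dropouts responding less often than completers, and on the split of dropout between arms. If every dropout is a failure, the planned 30-point difference would really be 24 points at 20% dropout in each arm. Type I error would stay at 5–6% with balanced dropout and reach about 13% at 25% versus 10%. With higher sham dropout the bias turns against the laser arm. These are illustrations, not forecasts.

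**What to change.** 1. In the dropout section, separate stopping treatment from leaving the trial. Leave the rules on when treatment stops as they are.
2. Keep collecting VAS, painkiller use, ODI, EQ-5D-5L and adverse events at the already scheduled Visits 9 and 10 from everyone who has not withdrawn consent.
3. Delete the incomplete-data criterion, because missing data should not be a reason to remove a participant.
4. Align the dropout, outcome and statistical sections on how discontinuation for an adverse event or SAE counts in the responder endpoint. This is a choice of estimand and should be written down as one.
5. Add a sensitivity analysis that counts every missing Visit 9 outcome as non-response. It belongs as a sensitivity analysis because it is not unbiased when some dropouts would have responded.

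The cost is a wording change, which under the quality control section needs review by the ministry and both ethics boards, plus a few extra follow-up contacts. Reported responder rates may be less favourable. The sample size need not change for this.

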### Outcome measurements

The primary outcome will be the between-group differences of the proportions of responders at 3 days after the intervention ends. A responder is defined as a participant who responds with more than 30% decrease in baseline VAS score without an increase in baseline use of painkillers (27, 28).

The secondary outcomes will include the between-group differences of changes in VAS, EQ-5D-5L, and ODI at 3 days after the treatment ends and 8 weeks after the treatment ends.

The VAS is a self-reported scale, usually a 100-mm-long straight line marked 0 for no pain and 100 for pain as intense as it could be (29). It is widely used to assess pain severity in LBP trials (30).

The EQ-5D is a generic assessment tool for measuring health-related quality of life (31). The EQ-5D-5L is a new version of the EQ-5D that extends the level of each dimension from three to five (32).

The ODI includes nine questions about interference with several physical activities and one question about pain intensity (33). We used the Korean version of the ODI, which excluded sexual life from the original ODI and has been validated (34).

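### The per-protocol exclusion rule has no time limit, so events after Visit 9 can remove valid Visit 9 data from the supplementary per-protocol analysis of the primary outcome

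*Protocol article*

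**What the plan says.** The section on dropout and violation criteria lists four grounds for dropout: "incomplete data that can affect the results of the trial"; a decision by the ethics board or principal investigator; withdrawal of consent; and "occurrence of a serious adverse event (SAE) causing requirement of hospitalization or surgery, serious disability, or death". None carries a date or visit. The consequence concerns the trial as a whole, not only treatment: "Participants who meet the dropout criteria will be discontinued from participating in our clinical trial". Treatment adherence is covered separately, as a violation: "participating in less than six of the eight treatment sessions (<75% compliance with the intervention protocol"). The section then closes with the rule at issue: "The participants who meet the violation and dropout criteria will be excluded from the per protocol set (PPS) analysis".

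On timing, the section on outcome measurements says: "The primary outcome will be the between-group differences of the proportions of responders at 3 days after the intervention ends". Table 1 places this at Visit 9 (week 4 plus 3 days). The secondary outcomes continue to Visit 10 at week 12: "changes in VAS, EQ-5D-5L, and ODI at 3 days after the treatment ends and 8 weeks after the treatment ends".

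The section on statistical analysis makes the FAS the primary population for efficacy and the PPS supplementary, with missing values handled by multiple imputation. It adds: "The results of the FAS and PPS analyses will be compared and reflected in the efficacy evaluation".

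**The concern.** A per-protocol analysis of an outcome should depend on what happened up to the time that outcome was measured. Here the only PPS described is cut by criteria that stay in force for about 7.6 weeks after the primary reading. Someone who attended all eight sessions and gave a valid Visit 9 pain score was fully per protocol for the primary outcome, yet a withdrawal or qualifying serious adverse event at week 9 takes that score out.

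Later leaving may also depend on the Visit 9 result. Study treatment has ended by then, and the section on interventions bars other treatment for the back pain throughout the study period, so non-responders plausibly have more reason to withdraw. The responder proportion in the PPS would then be shaped partly by the outcome itself. Because the FAS and PPS results are to be compared, a gap produced in this way could be taken for an effect of adherence.

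**Working it through.** **Reading the rule.** I take the rule to exclude anyone who meets either set of criteria. The dropout criteria end participation in the trial, and participation runs to week 12. Adherence has its own criterion, so the dropout criteria are not confined to the treatment period. The reach to week 12 is inferred from the absence of any limit; the text does not state it.

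**Reproducing the plan's sample size.** Inputs from the section on sample size estimation: 30% v 60% responders, two-sided alpha 0.05, power 0.80, maximum dropout 20%.

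- n = (1.96·√(2×0.45×0.55) + 0.842·√(0.30×0.70 + 0.60×0.40))² / 0.30² = 41.98, rounded up to 42 per arm.
- 42 / 0.80 = 52.5, rounded up to 53 per arm, 106 in total. Both figures agree with the plan.

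**PPS size and power.** Inverting the same formula, power = Φ[(0.30·√n − 1.96·√0.495) / √0.45]. If all 20% leave and all are excluded, n = 53 × 0.80 = 42.4 and power is 0.804. If only events up to Visit 9 counted, n = 42.4 + 10.6 × s, where s is the share of dropout that falls after Visit 9. The protocol does not give s, so its full range is shown:

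| Share s after Visit 9 | Extra participants per arm | PPS per arm | Power |
|---|---|---|---|
| 0% | 0 | 42.4 | 0.804 |
| 25% | 2.65 | 45.1 | 0.828 |
| 50% | 5.3 | 47.7 | 0.849 |
| 75% | 7.95 | 50.4 | 0.868 |
| 100% | 10.6 | 53.0 | 0.885 |

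The literal rule therefore costs the PPS between 0 and 0.885 − 0.804 = 0.081 in power. As one illustration, assume dropout spread evenly over 12 weeks. Then s = (12 − 4.43)/12 = 63%, or 6.7 per arm. The PPS is about 42 instead of 49 per arm and power about 80% instead of 86%. The 95% confidence interval half-width, 1.96·√(0.45/n), is 20.3 instead of 18.8 points.

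**Possible shift in the estimate.** Start from 16/53 (30.2%) sham and 32/53 (60.4%) laser responders, a difference of 30.2 points. Suppose that only non-responders leave after Visit 9:

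- Six from sham only: 16/47 = 34.0%; difference 26.3, down about 4 points.
- Six from laser only: 32/47 = 68.1%; difference 37.9, up about 8 points.
- Six from each arm: 68.1% − 34.0% = 34.0, up about 4 points.
- Twelve split in proportion to the non-responders in each arm (37 sham, 21 laser), so 12×37/58 = 7.7 and 12×21/58 = 4.3: 32/48.7 − 16/45.3 = 65.8% − 35.3% = 30.5, almost unchanged.

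A material shift thus needs non-responders to leave at different rates in the two arms.

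**The case against.** The strongest reply is that the text is merely silent. This is a condensed article, membership of the PPS by endpoint is often settled in the statistical analysis plan or at blinded data review, and limiting exclusion to events before the analysed visit would not contradict any sentence here. That carries weight and lowers the importance of the point. It does not dispose of it, because the article does more than omit a detail: it states an unrestricted rule for a single set. An analysis plan that follows the rule inherits the problem, and one that narrows it departs from the wording.

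Three stronger readings are tempting, and the documents do not support them.

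- A reader might infer that the trial's primary analysis is damaged. It is not: the FAS is primary, and the exclusion rule is stated only for the PPS.
- A reader might infer that missing Visit 10 is in itself enough for removal. The incomplete-data criterion applies only to gaps that can affect the trial's results, and missing values are to be imputed, so an absent week 12 value need not meet it. The withdrawal, serious adverse event and discontinuation cases do not rely on this criterion.
- A reader might infer that the PPS becomes underpowered. The 20% is a maximum already built into the 53 per arm, so what is lost is surplus above the planned 80%.

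It is also fair to say that the even-spread figure is only an assumption, since nine of the ten visits fall by week 4 plus 3 days, and that shifts of 4 to 8 points need an extreme one-arm pattern.

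**Conclusion.** The point stands as a minor one. Taken literally, the rule lets events after Visit 9 remove participants with adequate treatment and a valid primary reading from the supplementary PPS analysis of the primary outcome. The primary test, alpha and sample size do not change.

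The size cannot be fixed from the documents. It lies between 0 and 10.6 participants per arm and between 0 and about 8 points of PPS power, given 30% v 60% responders and total dropout at the stated maximum. About 80% power remains under the literal rule, provided that all PPS exclusions, including protocol violators, stay within that 20%. Any bias depends on unequal leaving by non-responders between arms, for which the protocol gives no figure. What remains is a risk to interpretation: a difference between FAS and PPS could reflect follow-up losses and not adherence.

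**What to change.** Define PPS membership per time point. For the responder outcome and the other Visit 9 outcomes, exclude only participants who met a dropout or violation criterion on or before Visit 9. For the week 12 outcomes, count criteria met up to Visit 10. Say explicitly that an event after Visit 9 does not remove a participant from the Visit 9 PPS. This concerns analysis sets only and leaves the dropout criteria as they are.

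The cost is a sentence or two in the PPS definition, two PPS flags in place of one, and two PPS denominators to report and explain. It needs no further participants, visits or data. If the statistical analysis plan already sets membership this way, the protocol wording should be brought into line with it.
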